### 5.2.3 Had unknown status (unknown)

Subjects who do not fall into either of the above Items 1) Had Breast Cancer or 2) Did not have Breast Cancer will be defined as Had unknown status. Subjects whose medical examination data in a report of breast cancer are not grasped will be classified into unknown.

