#### 9. Follow-up method

Follow-up is made using two methods, i.e., direct contact (interview and mail) with the subject (or her relative) and comparison with external data.

When communicating directly with subjects (or persons involved), at the point at which 20 months have passed since they underwent the first breast cancer screening, a sealed letter shall be sent to the subjects to encourage them to undergo a second breast cancer screening. During the second screening, the presence/absence of breast cancer diagnosed after the first screening is checked. For subjects who do not receive the second screening, the presence/absence of breast cancer diagnosed after the first screening is investigated over telephone.

Comparison with external data means checking for move-outs or death of subjects by means of access to the inhabitant register, access to the death slip to confirm death (and its cause) and access to regional cancer register to check for breast cancer among the subjects. The step to obtain approval of each comparison to external data is taken by the Central Data Center, and comparison is practiced after approval is obtained (refer to “8.5. Follow-up” for details).

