## 5.2 Rules for determining the presence or absence of breast cancer

Breast cancers were ascertained by diagnostic assessment of first and second screening results, hospital discharge records and cancer registry databases. Miyagi prefecture has a sophisticated system of local registration for cancer, which contains virtually all breast cancer patients' registration conducted in Miyagi prefecture. Therefore, it was possible to identify screening-detected cancer, interval cancers and not breast cancer exactly. The latest date for the censoring of data on breast cancer for the purpose of analysis will till February 2020.

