### 5.2.2 Did not have Breast Cancer (not breast cancer)

Subjects without breast cancer will be defined as those who do not meet the abovementioned Had Breast Cancer and meet any of the following criteria:

- Data at the second screening are inputted, and no breast cancer is reported.
- Questionnaire data are inputted, and no breast cancer is reported.
- Data at the second screening are missing (screening and questionnaire), but during an interval between the first to second screening, at least one detailed examination is performed, and the results of the detailed examination revealed no breast cancer.
- Subjects with a diagnosis of breast cancer after the screening interval specified in this study: Subjects who meet (2) TN, (4) TN, (6) FP or (8) FP outside the green frame.

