### 5.3 Data review in a blinded manner (Case ascertainment and validation)

Subjects with a diagnosis of breast cancer in this study will be defined as those with breast cancer recorded in the column for “Diagnosis” in the report of detailed examination results at the examined medical institution and images and pathological data supporting the diagnosis of breast cancer can be understood. After the input function of the EDC installed at each participating site is locked, the central data center should request each study site to submit copies of source documents on subjects with a diagnosis of breast cancer. In addition, the EDC screen capture of the database and documents, in which the randomized groups are blinded, for review should be also sent to the Study Group Secretariat.

It is a given fact that the classifications ((1) FN to (8) FP) of first screen-detected cancer and interval cancer in subjects with a diagnosis of breast cancer based on the statistical definitions are accurate and valid in reliable analyses. In order to secure the accuracy of classifications, data on subjects with a diagnosis of breast cancer will be reviewed by oncological surgeons ([name] and [name]) in a manner that the randomized groups are blinded.

Essential parameters for carrying out a logical check for the classifications ((1) FN to (8) FP) with SAS using the EDC database will be as follows: Assessment of comprehensive category at the first screening, date of screening (all entered volumes), date of detailed examination (all entered volumes), the results of the detailed examination (all entered volumes), information on the study site performing the detailed examination, the date of diagnosis, and the cause of the diagnosis of breast cancer reported in the questionnaire form (screening, medical examination due to subjective symptoms, and detailed examination [or follow-up] as part of screening performed during the screening period in the study).

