|--------------------------------------------|--------------------------------------------------------------------------------------------------------------|------------------------------------------------------------------------------|
| Detection rate of screening, %
(95% CI) | The number of cancers with a positive initial interpretation among 1,000 screening examinations.             |                                                                              |
| Sensitivity, %
(95% CI)                 | $\text{Sensitivity} = \frac{[5]\text{TP}+[7]\text{TP}}{[5]\text{TP}+[7]\text{TP}+[1]\text{FN}+[3]\text{FN}}$ | (Number of true positive assessments) / (Number of all positive assessments) |
| Specificity, %
(95% CI)                 | $\text{Specificity} = \frac{\text{TN}}{\text{TN}+\text{FP}}$                                                 | (Number of true negative assessments) / (Number of all negative assessments) |

365 The 95% CIs will be calculated using the binomial distribution method.

366 At the statistical analysis/ data monitoring committee meeting held on October 28, 2013, consensus was reached  
 367 that subjects having an unknown status would be excluded from the analyses of sensitivity and specificity.

368 7.2.2 Method of the primary analysis taking account of correlations within the cluster

369 All “screen-detected cancer,” “interval cancer” and “subjects without cancer” at the first screening to be used for  
 370 calculating sensitivity/ specificity, the primary endpoints, are binary outcomes. As an analysis method for  
 371 estimating the primary endpoints in the two groups, GEE taking account of correlations within the cluster will be  
 372 used. For estimation of the parameters, robust variance estimator with a compound symmetry structure as a  
 373 working correlation matrix will be employed.

374

375     **8. Statistical Analysis Rules**

| Item                                                                         |                                  | Display digit                                                                                                                                                                                                                                               |

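### Reported breast cancers without medical documentation leave the sensitivity denominator, and the SAP does not say whether a registry or discharge record alone makes a case

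*Combined protocol and SAP*

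**What the plan says.** Four SAP rules and one protocol procedure bear on who counts as a cancer.

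- **Sources (SAP 5.2).** "Breast cancers were ascertained by diagnostic assessment of first and second screening results, hospital discharge records and cancer registry databases". For Miyagi, where the registry is described as nearly complete, the section adds: "Therefore, it was possible to identify screening-detected cancer, interval cancers and not breast cancer exactly".
- **Case definition (SAP 5.3).** A subject with a breast cancer diagnosis is one with cancer in the diagnosis column of the "report of detailed examination results at the examined medical institution and images and pathological data supporting the diagnosis of breast cancer can be understood".
- **Unknown status (SAP 5.2.3).** "Subjects whose medical examination data in a report of breast cancer are not grasped will be classified into unknown". By the committee consensus recorded in SAP 7.2.1, it was agreed "that subjects having an unknown status would be excluded from the analyses of sensitivity and specificity".
- **No breast cancer (SAP 5.2.2).** For a woman not already classed as a case, one sufficient criterion is: "Questionnaire data are inputted, and no breast cancer is reported".
- **Follow-up (protocol 9).** For women who miss the second screening, "the presence/absence of breast cancer diagnosed after the first screening is investigated over telephone".

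The plan does not say whether a registry entry or discharge record alone satisfies SAP 5.3. It gives no number of unknowns and plans no sensitivity analysis for them.

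**The concern.** The evidence needed for a positive status differs from that needed for a negative one. A questionnaire without a reported cancer is enough for a woman to count as cancer-free. A questionnaire with a reported cancer, but without medical data behind it, makes her unknown and removes her from the analysis.

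The hurdle is unlikely to fall evenly on true positives and false negatives. Sites check, store and transmit the work-up results of recalled women (protocol 16.1, items 4 to 6), so a screen-positive cancer tends to arrive with the report that SAP 5.3 asks for. A class (1) false negative is by definition found outside screening, in a woman whose first screen was Category 2 or lower and who was not recalled from it. Her cancer comes to light through a questionnaire, a telephone call or the registry. Protocol 8.5 describes the registry check as yielding presence or absence of breast cancer and a date of onset, which is not a report with images and pathology.

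Sensitivity is a primary endpoint and the basis of the sample size. A case rule that removes false negatives more readily than true positives would raise it in each arm and alter the between-arm difference.

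**Working it through.** **Inputs.** From protocol section 3 and SAP 2.5: 63 cancers in 20,587 women over two years; control 45 screen-detected and 18 interval; intervention 54 and 9; two-sided 5%, power 80%; 130 cases and 42,500 women per group. The shares of cases lost are my assumption, because the documents give none.

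**The plan's own figure.** With p1 = 45/63 = 0.7143, p2 = 54/63 = 0.8571 and mean 0.7857:

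n = [1.960 × √(2 × 0.7857 × 0.2143) + 0.842 × √(0.7143 × 0.2857 + 0.8571 × 0.1429)]² / 0.1429² = 129 cases per group, against the stated 130. Then 130 / (63/20,587) = 42,481 women, against 42,500. Both reproduce.

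**Effect of lost cases.** Let f be the share of false negatives lost and g the share of true positives lost:

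sensitivity = TP(1 − g) / [TP(1 − g) + FN(1 − f)]

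This exceeds the full-data value only if f > g. If f = g, nothing changes (71.4% and 85.7%). If only true positives are lost, at 10%, it falls to 40.5/58.5 = 69.2% and 48.6/57.6 = 84.4%.

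**Interval cancers only, equal in both arms (g = 0):**

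| f | Control | Intervention | Difference (points) | Power at planned size |
|---|---|---|---|---|
| 0 | 45/63 = 71.4% | 54/63 = 85.7% | 14.3 | about 80% |
| 10% | 45/61.2 = 73.5% | 54/62.1 = 87.0% | 13.4 | about 77% |
| 20% | 45/59.4 = 75.8% | 54/61.2 = 88.2% | 12.5 | about 73% |
| 30% | 45/57.6 = 78.1% | 54/60.3 = 89.6% | 11.4 | about 68% |

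Power uses the remaining cases, scaled from 130 per group. At f = 20%, for example, these are 130/63 × 59.4 = 122.6 (control) and 130/63 × 61.2 = 126.3 (intervention).

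**Unequal loss (g = 0).** With 10% lost in control and 30% in intervention, the difference is 89.6 − 73.5 = 16.0 (from unrounded values). With 30% in control and 10% in intervention, it is 87.0 − 78.1 = 8.8 (likewise).

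**Two routes for a registry-only or discharge-only cancer.** If SAP 5.3 is applied literally, such a woman is not a case. With no second-screen, questionnaire or detailed-examination result she becomes unknown. With a clean second screening or questionnaire she meets SAP 5.2.2 and counts as cancer-free. Either way the cancer leaves the sensitivity denominator. If SAP 5.2 governs instead, she stays in. The text supports both readings.

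**The case against.** The strongest reply is that the plan is built to find and verify these cancers.

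- SAP 5.2 names registry and discharge records as sources, and a discharge record may itself supply the medical examination data that SAP 5.2.3 asks for.
- SAP 5.3 speaks of the institution that examined the woman, which need not be the screening site. Its review parameters include the questionnaire's cause of diagnosis, with symptomatic presentation listed, and it calls for source-document review in complicated cases, including women who report examinations outside the study.
- Table 1 of SAP 5.3 gives questionnaire and site data equal weight in separating screen-detected from interval cancers, and sends queries back to the site and medical institution for missing TNM and histology.
- SAP 5.4 treats three subjects with inadequate data as missing for stage and histology, which suggests that thin documentation did not automatically remove a case.
- Not every false negative arises outside screening: class (3) is found through screening, and class (5) true positives are found outside it.
- Verifying a self-reported cancer before counting it is a defensible case definition.

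Much of this stands. A reader might infer that every registry or discharge cancer is dropped; SAP 5.2 does not allow that conclusion, and the two sections are in tension. A reader might also infer that the lost cases are mostly interval cancers; that is plausible from the pathways, but no count supports it.

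It does not dispose of the point. Equal weighting in Table 1 concerns the split of recognised cases, not whether a case is recognised. The specified re-query is for TNM and histology. The three subjects in SAP 5.4 are not a count of cancers classed as unknown. The claim of exact identification in Miyagi holds only if registry cancers count as cases, which SAP 5.3 does not say.

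**Conclusion.** The rule plainly removes cancers known only by self-report from the sensitivity denominator. It leaves open whether cancers known only from the registry or a discharge record are kept, made unknown, or counted as cancer-free.

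Sensitivity is overstated in each arm if the proportion of false negatives lost exceeds that of true positives. The follow-up pathways make this likely but do not prove it. If 10-30% of interval cancers alone were lost, the overstatement would be 2.1 to 6.7 points in control (73.5 or 78.1 less 71.4) and about 1.2 to 3.8 points in intervention (from unrounded values). That range is assumed, and the actual loss could be smaller, particularly in the Miyagi data used for the breast-density analyses.

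A reader might go further and conclude that the rule flatters ultrasonography. The figures do not support that: equal interval-only loss shrinks the between-arm difference and costs power. Only unequal loss can enlarge it, and unequal loss can as easily reduce it. The documents give no information on loss by arm.

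**What to change.** 1. Reconcile SAP 5.2.1, 5.2.2 and 5.3. State that a breast cancer recorded in the regional registry or a discharge record within the window counts as a case and overrides a negative questionnaire. Require pathology only for the stage and histology analyses in SAP 5.4.
2. Assign these cases to classes (1) to (8) from first-screen overall category, diagnosis date and mode of detection. Mode is needed because SAP 5.1 uses different windows: 24 months if the cancer was not found through screening, the planned second-year screening if it was. A Category 2 woman diagnosed after 24 months but before her planned screening is (2) true negative or (3) false negative depending on mode. Where mode is not known, state a default and check the alternative.
3. Report the number of unknowns by arm and first-screen category, separating reported but undocumented cancers from women with no follow-up information.
4. Add a bounding analysis in which undocumented self-reported cancers count as false negatives or true positives according to first-screen category.

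The cost is SAP wording, one extra table and one extra analysis, largely on data already collected. The drawback is that a few unconfirmed self-reports enter the calculation, but only in the bounding analysis.

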### 5.3 Data review in a blinded manner (Case ascertainment and validation)

Subjects with a diagnosis of breast cancer in this study will be defined as those with breast cancer recorded in the column for “Diagnosis” in the report of detailed examination results at the examined medical institution and images and pathological data supporting the diagnosis of breast cancer can be understood. After the input function of the EDC installed at each participating site is locked, the central data center should request each study site to submit copies of source documents on subjects with a diagnosis of breast cancer. In addition, the EDC screen capture of the database and documents, in which the randomized groups are blinded, for review should be also sent to the Study Group Secretariat.

It is a given fact that the classifications ((1) FN to (8) FP) of first screen-detected cancer and interval cancer in subjects with a diagnosis of breast cancer based on the statistical definitions are accurate and valid in reliable analyses. In order to secure the accuracy of classifications, data on subjects with a diagnosis of breast cancer will be reviewed by oncological surgeons ([name] and [name]) in a manner that the randomized groups are blinded.

Essential parameters for carrying out a logical check for the classifications ((1) FN to (8) FP) with SAS using the EDC database will be as follows: Assessment of comprehensive category at the first screening, date of screening (all entered volumes), date of detailed examination (all entered volumes), the results of the detailed examination (all entered volumes), information on the study site performing the detailed examination, the date of diagnosis, and the cause of the diagnosis of breast cancer reported in the questionnaire form (screening, medical examination due to subjective symptoms, and detailed examination [or follow-up] as part of screening performed during the screening period in the study).

| Table 1. Blinded review and data check in subjects with a diagnosis of breast cancer for classifying them into detected and interval cancers (source documents and EDC data) |                                                                                                                                                                                                                                                                                                                                                                                                                                                                                                                                                                                                                                                                                                                                                                                                                                              |
|------------------------------------------------------------------------------------------------------------------------------------------------------------------------------|----------------------------------------------------------------------------------------------------------------------------------------------------------------------------------------------------------------------------------------------------------------------------------------------------------------------------------------------------------------------------------------------------------------------------------------------------------------------------------------------------------------------------------------------------------------------------------------------------------------------------------------------------------------------------------------------------------------------------------------------------------------------------------------------------------------------------------------------|
| Step 1                                                                                                                                                                       | Use SAS to perform a logical check of essential parameters in EDC data.                                                                                                                                                                                                                                                                                                                                                                                                                                                                                                                                                                                                                                                                                                                                                                      |
| Step 2                                                                                                                                                                       | 
Blind the randomized groups recorded in case result reports. Review the case by checking screening, detailed examination and the chronology of medical examination/ logics of the course.
 
For 1) subjects in whom breast cancer determined once is denied based on the results of a medical examination at a cancer base hospital, and 2) subjects who are found to be not having breast cancer because of mistakes with transcription in the CRF and input in the column for diagnosis, clean the data based on the facts, and specify the absence of breast cancer. Retain not only the SAS program but also correspondence tables and source documents.
 
* With regard to missing data on TNM Classification and histological classification, make inquiries again to the participating site and medical institution.
 |
| Step 3                                                                                                                                                                       | Cross-check the results of a review assessment and SAS program calculations.                                                                                                                                                                                                                                                                                                                                                                                                                                                                                                                                                                                                                                                                                                                                                                 |
| Step 4                                                                                                                                                                       | If the results in Step 3 are inconsistent, search for the reasons, and handle the matter through processes from an examination, discussion to agreement.                                                                                                                                                                                                                                                                                                                                                                                                                                                                                                                                                                                                                                                                                     |
| Step 5                                                                                                                                                                       | Determine the classification to be used for the analysis through the abovementioned examination processes.                                                                                                                                                                                                                                                                                                                                                                                                                                                                                                                                                                                                                                                                                                                                   |
| Comments                                                                                                                                                                     | For classification between screen-detected cancer and interval cancer, both screening data at the study site and data on a history of screening recorded in the questionnaire from by the study participants will be used so that the screening and questionnaire data have equal values.                                                                                                                                                                                                                                                                                                                                                                                                                                                                                                                                                    |

However, for some subjects with a complicated data structure, for example, 1) when there are both biennial screening specified in the study and annual screening, 2) the results of several follow-ups are entered as detailed examination data, or 3) subjects who report that they have undergone several screening sessions and/or medical examinations not specified in the study in the questionnaire form, accuracy cannot be sufficiently secured only by classification based on data logical checks using analysis software, SAS. Hence, overall verification activities such as cross-checking between source documents and inputted EDC data will be essential so that the source documents of subjects with a diagnosis of breast cancer should be reviewed.

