### 2010

- (1) Second screening: Performed on 35,000 subjects each from the above-mentioned group A2 and group B2.
- (2) First screening: Not performed

454 Table 1. Annual plan: Screening schedule

| Individual or cluster                             |         | 2007           | 2008           | 2009           | 2010           |
|---------------------------------------------------|---------|----------------|----------------|----------------|----------------|
| Ultrasound-combined
(intervention) group       | Group 1 | A1
(15,000) | A2
(35,000) | A1
(15,000) | A2
(35,000) |
|                                                   | Group 3 | None           | None           | A3
(10,000) | None           |
| Ultrasound-uncombined
(non-intervention) group | Group 2 | B1
(15,000) | B2
(35,000) | B1
(15,000) | B2
(35,000) |
|                                                   | Group 4 | None           | None           | B3
(10,000) | None           |

455

456 8. Survey and observation

457 8.1. At the time of enrollment (refer to Attachment 8)

458 (1) Name of subject

459 (2) Date of birth

460 (3) Address (prefecture, ward/city/town/village, street, house number)

461 (4) Telephone number

462 (5) History of malignancy: Present/Absent

463 If present, specify the site:

464 (6) Interview (history of breast cancer screening, history of menstruation, history of  
465 pregnancy and delivery, breast-feeding, familial history of breast cancer, history of  
466 breast surgery, presence/absence and nature of subjective symptoms)

467 - History of breast cancer screening: Absent/Present

468 If present, the year of latest screening:

469 Method of screening (clinical breast examination, mammography,  
470 ultrasonography)

471 - History of malignancy: Absent/Present

472 If present, specify the site:

473 - Subjective symptoms: Absent/Present

474 If present, specify the nature (mass, tenderness, others:)

475 (7) Group assigned: Intervention group /Non-intervention group

476

477 8.2. Information related to screening results

478 (1) Date of screening

479 (2) Name of the screening facility

480 (Mammography)

481 (1) Presence/absence of lesions, features of lesions (mass, calcification, others) and  
482 category (1, 2, 3, 4, 5), location of lesions  
483 (2) Separate assessment of right and left sides  
484 (Ultrasonography)

485 (1) Presence/absence of breast lesions (none, mass-forming lesions, non-mass forming  

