### 6.4.1 Verification of compliance with randomization

After the EDC input function at the site is locked, the key will be opened. System numbers issued by the central randomization and the randomized groups, and system numbers inputted in the EDC at the site and the randomized groups will be cross-checked using data received by the EDC system at the central data center, and inquiries on the following items should be made to each study site:

- (1) Verification of subjects incompliant with randomization who underwent screening different from that centrally randomized.
- (2) Verification of a system number that a number issued by central randomization is not entered in the EDC.
- (3) Verification of subjects for whom numbers different from those assigned by the central data center are inputted in the EDC.

- (4) Verification of a system number that has been entered once but deleted.
- (5) Double entry
- (6) Subjects whose date of consent for the study participation is after the date of screening.

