##### (2) Subjects with inadequate test (deviation)

- i. Subjects in the intervention group who have no ultrasonographic data.
- ii. Subjects in the non-intervention group whose ultrasonographic data are inputted.

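### The cancer-case review is called blinded, but only the group label is stated to be masked, and nothing requires the classification to be locked before the allocation key is opened

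*Combined protocol and SAP*

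**What the plan says.** **What is masked.** Under SAP 5.3, once the EDC input function is locked at the sites, the data center requests copies of source documents for cancer cases. For the review, "the EDC screen capture of the database and documents, in which the randomized groups are blinded, for review should be also sent" to the Secretariat. Surgeons then review the cases "in a manner that the randomized groups are blinded". Table 1, Step 2 repeats the instruction: "Blind the randomized groups recorded in case result reports".

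**What is reviewed.** The next instruction in Step 2 is: "Review the case by checking screening, detailed examination and the chronology of medical examination/ logics of the course". For cases with a complicated data structure, SAP 5.3 finds SAS logic checks insufficient and adds that "the source documents of subjects with a diagnosis of breast cancer should be reviewed".

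**What the screening record holds.** Protocol 8.2 gives ultrasonography its own block of fields: lesions, their features, the examiner's category and the judging physician's category. SAP 6.4.4(2) shows that ultrasonography data are held in the EDC. It lists as deviations intervention subjects without such data and "Subjects in the non-intervention group whose ultrasonographic data are inputted".

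**When the key opens.** SAP 6.4.1: "After the EDC input function at the site is locked, the key will be opened". The stated purpose is a check of compliance with randomisation at the central data center.

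**The concern.** The review fixes which cancers enter the numerator and denominator of sensitivity. If the surgeons see the first-screen pages, masking the group entry does little, because ultrasonography was performed at the first screen in one arm and, deviations apart, not in the other. The SAP masks more fully elsewhere: in 5.5 the breast density readers are kept from screening results, work-up and follow-up data.

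The order of steps is also open. Collection of review documents and opening of the key both follow the EDC lock. Step 4 settles disagreements between the review and SAS by discussion until agreement, and Step 5 fixes the class. Neither is required to be finished before the key is open, and no rule keeps those involved away from it.

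At stake are some bias in the estimated sensitivity difference and a claim of blinding that the written procedure does not fully support.

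**Working it through.** **1. Where judgement can act.** SAP 5.1 defines eight classes.
- The overall first-screen category separates FN/TN (Category 2 or lower) from TP/FP (Category 3 or higher). It is recorded at screening, and the review does not re-read the first screen.
- Route and timing of detection separate FN from TN, and TP from FP. The limit is 24 months for cancers found outside screening and the planned Fiscal Year 2 screening for cancers found through screening.
- The complicated cases named in SAP 5.3 (annual as well as biennial screening, several follow-ups, self-reported extra sessions) bear on route and timing. Table 1 gives site data and questionnaire history equal weight, so a conflict between them needs a decision.
- Under SAP 5.2.1 and 5.2.2, TN and FP cancers do not count as cancers for sensitivity. The judgement therefore decides whether a cancer is counted at all.

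**2. The plan's figure.** Inputs from SAP 2.5 and protocol section 3: p1 = 45/63 = 71.4%, p2 = 54/63 = 85.7%, two-sided 5%, power 80%. With pooled variance and no continuity correction:

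n = [1.96 × √(2 × 0.7857 × 0.2143) + 0.8416 × √(0.2041 + 0.1224)]² / 0.1429² = 129 per group, against the stated 130.

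130 / (63/20,587) = 42,481, against the stated 42,500 per group. So 130 is a per-group number, and the planned difference is 14.3 points.

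**3. Illustration.** Assume 130 cancers per arm at the planning values: TP = 111.4 in the intervention arm and 92.9 in the control arm. Make three calls per arm, all favouring ultrasonography.

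| Calls | Sensitivity after | Change |
|---|---|---|
| Intervention, 3 FN to TN | 111.4/127 = 87.7% | +2.0 |
| Control, 3 TP to FP | 89.9/127 = 70.8% | −0.7 |
| Control, 3 TN to FN | 92.9/133 = 69.8% | −1.6 |

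The shift in the difference is 2.0 + 0.7 = 2.7 points, or 2.0 + 1.6 = 3.6 points. That is 2.7/14.3 = 19% to 3.6/14.3 = 25% of the planned effect. If the intervention calls were FP to TP instead, that arm would gain only 114.4/133 − 85.7% = 0.3 points, so the range above rests on FN-to-TN calls there.

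**4. Could a few calls create significance?** Start from no difference, 93/130 in each arm, and move only intervention cancers from FN to TN. It takes 17 moves (93/113 against 93/130, z = 1.97) to reach two-sided p < 0.05.

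**5. Order of steps.** SAP 5.3: EDC lock, document request, Steps 1 to 5. SAP 6.4.1: EDC lock, key opened. No sentence in either section links Step 5 to the opening of the key.

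**The case against.** The strongest reply is that the process is largely rule-based. SAS computes the classification from overall category, dates, results and cause of diagnosis. Step 3 cross-checks the review against it, and Step 4 requires the reasons for any discrepancy to be sought. Step 2 allows a reported cancer to be cancelled in only two factual situations: denial after examination at a cancer base hospital, or a transcription or input error. All of this stands and limits the room for bias. It does not remove it, because SAP 5.3 itself says that logic checks are not enough for complicated cases.

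Three stronger readings are tempting and not supported:
- A reader might infer that the surgeons are unblinded by the key. No section gives it to them. Its stated use is a compliance check at the data center, so the defect is a missing order of steps.
- A reader might infer that they certainly see the ultrasonography pages. The SAP does not say so. It follows only from what is not masked, and a manual outside these documents could redact more. Given the deviations in SAP 6.4.4, the marker is also imperfect.
- A reader might infer that the review can move cancers between TP and FN, at 100/130 = 0.77 points each. That split follows the recorded category, so only correction of a documented error would change it.

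It can also be said that protocol section 18 reports the main sensitivity comparison as already done, so a new order of steps may come too late for it. That is fair. It leaves open any classification made under the current SAP, whose data cut-off is February 2020.

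**Conclusion.** The point holds as a gap in the written procedure, and fixing it is a worthwhile, inexpensive improvement. The masking described covers the randomised group only, the fields that nearly reveal the arm are not withheld, and the classification need not be locked before the key opens. The plausible effect is a modest bias in the sensitivity difference. The 2.7 to 3.6 points are an illustration, resting on 130 cancers per arm, the planning sensitivities and six calls all in one direction. The documents give no count of judged cases, so the actual size is unknown. Nothing here shows that the review was in fact unblinded, and a few calls would not produce a significant result from no difference.

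**What to change.** - **SAP 6.4.1:** open the key only after the Step 5 classification is signed and locked. Failing that, keep it from everyone involved in Steps 2 to 5 until then. For classifications already completed, state the order that was followed.
- **SAP 5.3:** withhold the modality-specific first-screen pages from the reviewing surgeons. Give them overall category, dates, route to diagnosis, work-up and pathology. The essential parameters listed in 5.3 include no first-screen item other than the overall category and the screening date, so the classification rules lose nothing.
- **Source-to-EDC check:** SAP 5.3 calls this check essential. For the first-screen pages, assign it to data center staff outside the review.
- **Wording:** say that masking remains partial, because work-up records may hint at the modality that prompted recall.

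The cost is redaction for the cancer cases, an occasional query to the data center for a lesion detail, and a change in the order of two steps.
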